#### Data collection

Data will be collected at three points (see Table 1).

**Table 1 T1:** SIXES study visit schedule

	**Baseline (T0)**	**1-year follow-up (T1)**	**5-year follow-up (T2)**
Check inclusion/exclusion criteria	**X**		
Complete child’s assent and parental consent forms	**X**		
Randomization via website	**X**		
**Case report form to be completed by dentist**			
Baseline demographic information	**X**		
Dental history	**X**		
Record intervention or control arm	**X**		
Record side of treatment (right or left)	**X**		
Record stage of development of lower second molar	**X**		
Record type of anesthetic/sedation used	**X**		
Record dental treatment to remaining upper first permanent molars	**X**	**X**	**X**
Record orthodontic treatment since intervention		**X**	**X**

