### Interventions

The patient will continue to have all other treatment planned and carried out as normal. The only difference in treatment will be related to the FPM extractions (one side only per patient will be entered into the trial). For patients allocated to the control arm, both the upper FPM and lower FPM will be extracted. For patients in the intervention arm, only the lower FPM will be extracted.

Only one side of the mouth will have data collected for the study. For patients who require extraction of lower FPMs on both sides of the mouth, the decision of which side to include in the study will be taken through randomization.

The control group will have the normal standard intervention according to the current standard guidelines, and will receive routine patient care with the normal practice of compensation extraction, while the intervention group will have removal of their lower FPMs but no compensation extraction of the upper FPM will be carried out.

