### Participant recruitment and retention

Patients who meet the inclusion criteria will receive an invitation to take part in the trial will be identified during attendance at appointments with clinicians participating in the trial.

It is anticipated that the majority of patients will be attending for a six monthly routine check-up appointment (primary care GDP or community dentist) or a non-urgent secondary care assessment (practice-based specialist orthodontist, hospital-based orthodontic service and pediatric department).

Patients attending for routine check-up appointments or non-urgent assessments, who meet the inclusion criteria, will be assessed by the dentist for eligibility, and asked whether they wish to participate when they return for treatment at their next appointment. The patients and parents will be given information on the study to take home with them. Consent will be taken at the subsequent appointment by a dentist participating in the trial as a principal investigator (PI). Randomization will be carried out prior to this appointment and treatment.

For children who attend for urgent appointments, presenting in pain, the patients and their parents will also be approached at the time of their appointment about whether they wish to participate in the study. Because there is the need to alleviate the child’s symptoms as soon as possible, usually involving extraction of the tooth, there is no scope for 24 hours to reflect on the trial information. For this reason some patients will be invited to participate at their assessment appointment. Consent and randomization will still follow best practice, and parents and patients will still be given time to look at the patient information sheets and consider the study. The intervention in this study (extraction of a single tooth compared with extraction of two teeth) still allows the patient to return for conventional treatment (extraction of the upper FPM) should they be allocated to the intervention arm but change their mind about participation at a later date.

On enrollment to the SIXES trial, parents and patients will be given ‘calling cards’ saying that they are participating in the study, with details of their dentists and who to contact regarding the study.

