#### Secondary outcomes

The secondary outcomes for the study are:

1. position of the upper FPMs with regard to over-eruption^a^;

2. residual spacing between the lower second permanent molar and the lower second premolar^a^;

3. American Board of Orthodontics (ABO) scores^a^;

4. type of anesthetic used during procedures^b^;

5. dental or orthodontic treatment carried out during the follow-up period^b^ ;

6. Child and Parent Oral Health-Related Quality of Life (OHRQoL) scores (child and parent questionnaires).

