**Other clinical records**			
Dental impressions and occlusal registration	**X**	**X**	**X**

At time of extraction (T0):

1. Dental impressions and a record of occlusal registration will be taken for study models

2. The dentists will complete a case report form (CRF) (patient details, which arm randomized to, which side treatment was allocated to, what kind of anesthetic was used - local anesthesia (LA)/inhalation sedation (IHS)/general anesthesia (GA)/other type of sedation)

3. Children’s Oral Health-Related Quality of Life (OHRQoL) questionnaire

4. Parental OHRQoL questionnaire

After 1 year (T1):

1. Dental impressions and a record of occlusal registration will be taken for study models

2. Record of any dental treatment (to remaining upper FPMs) or orthodontic treatment provided since initial intervention

3. Children’s OHRQoL questionnaire

4. Parental OHRQoL questionnaire

After 5 years or when child turns 14 (whichever is first) (T2):

1. Dental impressions and a record of occlusal registration will be taken for study models

2. Dentists will record any dental treatment (to remaining upper FPMs) or orthodontic treatment provided since initial intervention

3. Children’s OHRQoL questionnaire

4. Parental OHRQoL questionnaire

The CRFs and questionnaires will all be marked with the patient’s unique study ID number which will be linked to the enrollment log for the trial.

Study models will be 3D scanned to measure occlusal changes. All patients’ lower study models will be assessed with regard to the tipping of the lower second permanent molar relative to the occlusal plane. The scanning software will be able to create an occlusal plane from cusp tips in order to calculate the degree of molar tipping. Not all patients will have an erupted lower second permanent molar at the earlier time points in the study.

Only the groups of patients who do not have the upper FPMs extracted will require their upper study models to be assessed for FPM over-eruption. Each patient’s upper models will be superimposed on the palatal rugae and any movement in the *x, y* and *z* plane of the upper FPMs will be recorded.

In addition, the 3D scans of the models will be used to give ABO occlusal index scores and to assess and measure any residual spacing between the lower second permanent molar and the lower second premolar.

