#### Type of anesthetic

Data will be collected through the CRF on the type of anesthetic used during the extraction of FPMs (for example, whether any form of sedation or general anesthetic was used for each of the teeth extracted).

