#### Orthodontic/dental review

The dentist will complete a questionnaire regarding dental and orthodontic treatment at 1 year follow-up and final follow-up to find out whether:

1. the upper FPM is still present (for participants in the intervention group);

2. the upper FPM has required dental treatment and if so, details of the treatment (for participants in the intervention group);

3. the patient had, or are they currently undergoing, any orthodontic treatment? (If yes, the type of treatment);

4. they have experienced any symptoms of temporo-mandibular joint dysfunction syndrome (jaw pain).

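### Anesthetic type is scheduled at T0 only, and follow-up dental treatment only for upper first molars, so neither total anesthetic use nor the dental half of outcome 5 can be compared fairly between arms

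*Protocol article*

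**What the plan says.** *Anesthetic.* Secondary outcome 4 is "type of anesthetic used during procedures". The section on type of anesthetic defines the data as the "type of anesthetic used during the extraction of FPMs", tooth by tooth, and sets no end date. In Table 1 the row "Record type of anesthetic/sedation used" is marked under T0 and blank under T1 and T2. The lists under Data collection agree: the T0 list asks "what kind of anesthetic was used - local anesthesia (LA)/inhalation sedation (IHS)/general anesthesia (GA)/other type of sedation", and the T1 and T2 lists do not mention anesthetic. Under Participant recruitment and retention, the protocol notes that a child allocated to the intervention arm may later change their mind, and that the design "still allows the patient to return for conventional treatment (extraction of the upper FPM".

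*Treatment during follow-up.* Secondary outcome 5 is "dental or orthodontic treatment carried out during the follow-up period". Table 1 and the T1 and T2 lists restrict the dental part to remaining upper FPMs but do not restrict it by arm. The Orthodontic/dental review section asks whether "the upper FPM has required dental treatment and if so, details of the treatment (for participants in the intervention group", and restricts the question on presence of the tooth in the same way. Its questions on orthodontic treatment and jaw symptoms carry no arm restriction.

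*Analysis.* Data management and statistical methods lists both anesthetic use and dental/orthodontic treatment among the comparisons of intervention with control.

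**The concern.** Anesthetic burden is one of the stated reasons for the trial: the Abstract and the Introduction both argue that an additional extraction may move a child from local to general anesthesia. If a child spared the upper extraction at T0 has it later under sedation or general anesthesia, the early saving is partly or wholly undone. As scheduled, the forms would show that the tooth has gone but not how it was removed. The return route that the protocol describes exists in one arm only, so this gap is not symmetric.

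The treatment outcome has a different problem. A child whose trial-side upper FPM was extracted at T0 cannot have it treated during follow-up. A between-arm test of upper FPM treatment then mostly reflects which arm kept the tooth. An analysis plan can repair neither point afterwards if the data were never collected.

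**Working it through.** The protocol gives no figure to reproduce, so the check sets the sections side by side and then illustrates size under stated assumptions.

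**1. Anesthetic: scope against schedule**

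| Place | What it covers |
|---|---|
| Secondary outcomes, item 4 | Procedures, no time limit |
| Type of anesthetic | Each FPM extracted, no time limit |
| Table 1 and the T0/T1/T2 lists | T0 only |
| Participant recruitment and retention | Later upper FPM extraction possible, intervention arm |
| Withdrawal procedures | Children given alternative treatment by the clinician stay in follow-up and analysis |

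At T0 both arms are recorded on the same form at the same moment, so that comparison is randomized and symmetric. Anything after T0 is unscheduled.

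**2. Size of the undercount for cumulative use**

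Let *f* be the share of intervention-arm children who later have the upper FPM extracted, and *g* the share of those who have sedation or general anesthesia then but did not at T0. The undercount in the intervention arm is *f* × *g*. Both values are assumptions; the protocol gives neither. In percentage points:

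| *f* | *g* = 25% | *g* = 50% | *g* = 75% |
|---|---|---|---|
| 0% | 0 | 0 | 0 |
| 2% | 0.5 | 1.0 | 1.5 |
| 5% | 1.25 | 2.5 | 3.75 |
| 10% | 2.5 | 5.0 | 7.5 |
| 20% | 5.0 | 10.0 | 15.0 |

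With the 150 per group under Target sample size, *f* = 10% and *g* = 50% means 150 × 0.10 × 0.50 = 7.5 children. On this route the error runs one way, in favor of leaving the upper molar. Later FPM extractions elsewhere in the mouth would be missed in both arms, and the protocol gives no reason to expect different rates there.

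**3. Dental treatment: who can have an event**

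Under Interventions, controls lose both the upper and lower FPM on the trial side. The inclusion criteria require upper FPMs that are sound or restorable.

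- On the Orthodontic/dental review wording, only the intervention arm is asked, so controls contribute nothing.
- On the Table 1 wording, both arms are recorded. If the other-side upper FPM is kept, an intervention child has two upper FPMs that could be treated and a control has one. If it is removed in normal care, the counts are one and zero.

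With the same chance *q* of treatment per tooth, expected treated teeth per child are 2*q* against *q*, or *q* against 0. The arms differ even when the trial has no effect on any remaining tooth.

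**4. Orthodontic treatment**

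Table 1, the T1 and T2 lists and the Orthodontic/dental review section all collect this with no arm restriction. That half of outcome 5 is comparable.

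**The case against.** The strongest reply is that outcome 4 may mean only the initial procedure. T0 recording matches the rationale about planning that visit, and the stated objective is occlusion and oral health-related quality of life, not lifetime anesthetic burden. On that reading nothing is biased. This stands for the T0 comparison. It does not settle the matter, because neither outcome 4 nor the section on type of anesthetic states that limit.

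A second reply is that the follow-up questionnaire asks for details of upper FPM treatment, and the actual form may capture the anesthetic there. That is possible, but the published schedule does not provide for it. A third is that the return route is for children who reconsider participation, and some who withdraw will not be contacted again. This also stands: added fields would miss them.

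A reader might go further in four ways that the document does not support:

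- *That both between-arm comparisons are biased as collected.* The T0 anesthetic comparison is not, and the unequal dental comparison comes mainly from the intervention itself rather than from the form.
- *That upper FPM treatment is asked in one arm only throughout.* Only the Orthodontic/dental review section says so; Table 1 and the T1 and T2 lists do not.
- *That the anesthetic advantage could reverse.* Assuming general anesthesia at T0 in 40% against 50%, and a later rate *r* among the other 60% of intervention children, the cumulative difference is 0.50 − (0.40 + 0.60*r*): 7, 4 and −2 points at *r* = 5%, 10% and 20%. The sign changes only at the highest assumed rate, and nothing in the protocol anchors any of these values.
- *That with two lower molars to extract, the contrast becomes three against four teeth.* The Interventions section says only that "The patient will continue to have all other treatment planned and carried out as normal". It does not say the other side is compensated. The arms would still differ by one tooth and remain randomized, so this would be dilution rather than bias.

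**Conclusion.** The point holds in limited form, for two secondary outcomes.

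- Anesthetic use at the initial extraction is validly compared. Cumulative use is not, because later use would be undercounted in the intervention arm. The size is unknown: zero if no child returns, and 0.5 to 15 percentage points over the assumed non-zero values shown above.
- The dental half of outcome 5 is narrower in collection than in definition, is described inconsistently between sections, and is structurally unequal between arms. The orthodontic half is sound.

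The direction of the anesthetic error rests on the protocol's own statement that later upper FPM extraction is open to intervention-arm children. It does not rest on any assumed rate.

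**What to change.** 1. Add to the T1 and T2 forms, in both arms, the anesthetic or sedation type and the date for any FPM extraction since the last visit.
2. Report anesthetic use at the initial procedure and cumulatively to T2 as two separately labelled comparisons.
3. Reconcile Table 1 and the T1 and T2 lists with the Orthodontic/dental review section on which arms are asked about upper FPMs.
4. For outcome 5, compare arms on treatment that any child can have: any further extraction and any orthodontic treatment. Report upper FPM treatment descriptively in the intervention arm.

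The cost is a slightly longer form at visits already planned, with matching wording in the outcome definitions. Children who withdraw from contact will still be missed, so the cumulative comparison should report how many in each arm have incomplete follow-up.

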**Questionnaires**			
Child’s oral health quality of life questionnaire	**X**	**X**	**X**
Parental oral health quality of life questionnaire	**X**	**X**	**X**
**Other clinical records**			
Dental impressions and occlusal registration	**X**	**X**	**X**

At time of extraction (T0):

1. Dental impressions and a record of occlusal registration will be taken for study models

2. The dentists will complete a case report form (CRF) (patient details, which arm randomized to, which side treatment was allocated to, what kind of anesthetic was used - local anesthesia (LA)/inhalation sedation (IHS)/general anesthesia (GA)/other type of sedation)

3. Children’s Oral Health-Related Quality of Life (OHRQoL) questionnaire

4. Parental OHRQoL questionnaire

After 1 year (T1):

1. Dental impressions and a record of occlusal registration will be taken for study models

2. Record of any dental treatment (to remaining upper FPMs) or orthodontic treatment provided since initial intervention

3. Children’s OHRQoL questionnaire

4. Parental OHRQoL questionnaire

After 5 years or when child turns 14 (whichever is first) (T2):

1. Dental impressions and a record of occlusal registration will be taken for study models

2. Dentists will record any dental treatment (to remaining upper FPMs) or orthodontic treatment provided since initial intervention

3. Children’s OHRQoL questionnaire

4. Parental OHRQoL questionnaire

The CRFs and questionnaires will all be marked with the patient’s unique study ID number which will be linked to the enrollment log for the trial.

Study models will be 3D scanned to measure occlusal changes. All patients’ lower study models will be assessed with regard to the tipping of the lower second permanent molar relative to the occlusal plane. The scanning software will be able to create an occlusal plane from cusp tips in order to calculate the degree of molar tipping. Not all patients will have an erupted lower second permanent molar at the earlier time points in the study.

Only the groups of patients who do not have the upper FPMs extracted will require their upper study models to be assessed for FPM over-eruption. Each patient’s upper models will be superimposed on the palatal rugae and any movement in the *x, y* and *z* plane of the upper FPMs will be recorded.

In addition, the 3D scans of the models will be used to give ABO occlusal index scores and to assess and measure any residual spacing between the lower second permanent molar and the lower second premolar.

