## Background

### Introduction

The first permanent molars (FPMs) are the permanent teeth most commonly assessed as having a poor prognosis due to them being the permanent teeth most susceptible to dental caries in childhood [1,2] and the high prevalence of molar-incisor hypomineralization (MIH) [3,4]. It is accepted that while forced extraction of FPMs is rarely ideal, with appropriate timing and case selection, it can result in an acceptable occlusion for the child [5,6]. Preferably, all cases where planned loss of FPMs is anticipated should be managed jointly with an orthodontist, but this is not always possible. Treatment planning is complicated by the need to consider other factors alongside occlusal aspects such as the possible absence of other permanent teeth, the prognosis of the remaining molars, the anticipated cooperation of the child with any proposed restorative treatment, and socioeconomic factors. In addition, FPM teeth are the largest in the dentition, and their successful extraction places demands on both the child and the clinician.

To assist dentists in treatment planning, a national guidance document is available [7]. As well as advice on timing of extractions, this guidance recommends that in Class I and Class II cases, the extraction of a mandibular FPM should be compensated by the extraction of the opposing maxillary FPM. The rationale for compensating the extraction of a lower FPM is that an unopposed maxillary FPM may over-erupt and prevent mesial migration of the erupting lower second permanent molar. However, it has been suggested that there is little evidence to support this being a significant risk [8]. Furthermore, the extraction of an additional FPM places an increased burden on both the child and the dental team providing care for them, and may tip the balance of decision as to whether the extractions can be carried out under local anesthesia, towards favoring dental general anesthesia [9].

In summary, current clinical guidelines state that when a lower FPM is extracted, the upper FPM should also be extracted, yet this recommendation is based on little or no evidence. This randomized clinical trial will provide the evidence to answer this question: Is it necessary to extract the upper FPM routinely when extracting the lower FPM in the mixed dentition in order to prevent over-eruption of the upper FPM, which can cause occlusal problems?

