#### Data management and statistical methods

Anonymized cast models will be 3D scanned and process data analyzed to record the type and extent of dental treatment (including the study interventions) that the subjects have received during the period of the study. This will be entered into a GCP compliant data management system Open Clinica (https://www.OpenClinica.com), which can be exported to SPSS (Statistical Package for Social Sciences, Inc., Chicago, IL, USA) v.18 for statistical analysis. Patient satisfaction questionnaires will be entered into Open Clinica and exported to SPSS for descriptive statistical analysis.

COHQoL data will be entered into Open Clinica and exported to SPSS for quantitative analysis of differences in overall and domain scores at the three time points using Friedman test for repeated measures

For between group comparisons, data will be checked for normality of distribution and any evidence of skewness. Descriptive statistics will be prepared. Appropriate parametric or non-parametric analysis allowing for any clustering effect will be undertaken to determine statistically significant differences in the outcomes listed above between the two study groups including chi-squared and *t*-tests, if normally distributed.

The proposed analyses will investigate comparisons between the intervention group, where patients have not had compensatory removal of FPMs, and the control group where patients have had this done. Specifically, we are looking for clinically significant improvement in:

•position of second permanent molars (if erupted);

•degree of tipping of the lower second permanent molars;

•spacing between lower second premolar and second permanent molars;

•position/over-eruption of upper FPM in the intervention group;

•ABO scores;

•dental/orthodontic treatment required during the study period;

•child OHQoL scores;

•use of anesthetics.

Missing data will be analyzed by multiple imputation up to the patient’s last recorded visit.

Interim analyses will not be carried out for this study as it will not be possible to measure the primary outcome until recordings are taken at 5-year follow-up, by which time patient recruitment will be complete.

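### Upper-molar over-eruption has no control-arm value and no opposed reference tooth, so the listed comparison cannot be made and normal eruption cannot be separated from over-eruption

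*Protocol article*

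**What the plan says.** All references are to the protocol article.

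- **Secondary outcomes** lists the position of the upper first permanent molars (FPMs), with regard to over-eruption, as item 1, without restricting it to an arm.
- **Interventions** states: "For patients allocated to the control arm, both the upper FPM and lower FPM will be extracted". The same section confines data collection to one side of the mouth, chosen by randomisation when both lower FPMs are to be extracted.
- **Data collection** (text after Table 1) states: "Only the groups of patients who do not have the upper FPMs extracted will require their upper study models to be assessed" for over-eruption. On the method it says: "Each patient’s upper models will be superimposed on the palatal rugae and any movement in the" x, y and z plane is recorded. No opposed reference tooth is named.
- **Data management and statistical methods** introduces its list of analyses thus: "The proposed analyses will investigate comparisons between the intervention group, where patients have not had compensatory removal of FPMs, and the control group", and continues: "Specifically, we are looking for clinically significant improvement in". One item in that list is "position/over-eruption of upper FPM in the intervention group". The Abstract also describes over-eruption as an outcome in the intervention group.
- **Introduction** frames the trial question as whether routine upper extraction is needed "in order to prevent over-eruption of the upper FPM".

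**The concern.** Two things do not fit. First, the outcome sits in a list introduced as a contrast between arms, but one arm has no tooth to measure. Improvement relative to control has no meaning for this item.

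Second, the one-arm quantity that remains is displacement from baseline in growing children. A first molar can move relative to the palatal rugae as the child grows, whether or not it has an opponent. Without a tooth that kept its opponent, the trial can report that the upper molar moved, but not how much of that movement came from losing the lower molar. Over-eruption is the stated rationale for compensating extraction. Readers will look to this outcome to judge that rationale, and movement due to growth could be read as support for extraction.

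**Working it through.** **Step 1: where a value can exist.** The inclusion criteria allow one or two lower FPMs to be extracted. Setting Interventions beside Data collection, for children treated as allocated:

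| Arm and case | Trial-side upper FPM | Opposite-side upper FPM |
|---|---|---|
| Intervention, one lower FPM out | Kept, unopposed, measured | Expected present and opposed; outside the one-side rule |
| Intervention, two lower FPMs out | Kept, unopposed, measured | Has lost its opponent; no reference |
| Control, one lower FPM out | Extracted; no value | Expected present and opposed; outside the one-side rule |
| Control, two lower FPMs out | Extracted; no value | Has lost its opponent; no reference |

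The trial-side column has no control entry. A few control children may keep the tooth, because Withdrawal procedures allows the clinician to depart from allocation. They would be a self-selected group, and their upper molar would also be unopposed, so they are no comparator.

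**Step 2: what the measured quantity contains.** Let g be mean ordinary movement over follow-up and e the mean excess due to the lost opponent.

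- Trial side, intervention arm: mean movement = g + e.
- Opposite side, opposed: mean movement = g, if the two sides would otherwise move alike.
- Trial side minus opposite side = (g + e) − g = e.

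The plan as written supplies only the first line, which is one equation in two unknowns.

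**Step 3: time for g to accumulate.** Entry is at 7 to 11 years, and final follow-up is at five years or age 14, whichever is first. A child entering at 7 is measured at 12 (5 years) and one entering at 9 is measured at 14 (5 years). One entering on the eleventh birthday is followed for 14 − 11 = 3 years, and one just short of 12 for about 14 − 12 = 2 years.

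**Step 4: illustration with assumed values.** The documents give neither g nor a standard deviation, so both are assumed here. Take n = 150 (the planned evaluable number per arm in Target sample size), e = 0, and a two-sided 5% test of mean movement against zero:

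se = SD/√150; probability of significance = Φ(g/se − 1.96) + Φ(−g/se − 1.96)

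| Assumed g | SD 0.5 mm | SD 1.0 mm | SD 1.5 mm |
|---|---|---|---|
| 0 mm | 5% | 5% | 5% |
| 0.1 mm | 69% | 23% | 13% |
| 0.25 mm | 100% | 87% | 53% |
| 0.5 mm | 100% | 100% | 98% |

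Worked cell: g = 0.25, SD = 1.5 gives se = 1.5/12.25 = 0.122, g/se = 2.04, and Φ(0.08) = 53%.

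A cut-off behaves similarly. If movement above 1 mm were called over-eruption, the share of children labelled is 1 − Φ((1 − g)/SD). Over SD 0.5 to 1.5 mm that is 2% to 25% at g = 0, 16% to 37% at g = 0.5 mm, and 50% at g = 1.0 mm.

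The protocol states neither this test nor this cut-off. The illustration shows only that a one-arm summary responds to g even when e is zero.

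**Step 5: the protocol's own literature.** Under the heading on whether unopposed molars over-erupt, one cited cross-sectional adult study reports a mean of 1.44 mm more over-eruption than in controls with opposing molars. That figure is a difference from opposed teeth, the kind of quantity missing here.

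**The case against.** **The text is openly one-arm.** The list item, the Abstract and the Data collection section all confine over-eruption to children who keep the tooth. A reader might infer that the investigators intend an impossible two-arm test. The documents do not support that: the item's own wording points the other way, and the fault lies in a list lead-in and an aim of improvement that do not fit the item. This stands, and it reduces the first half of the point to a drafting conflict.

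**No rule says all movement counts as over-eruption.** A reader might infer that normal eruption will be counted as over-eruption. Data collection says only that movement is recorded. A threshold or derivation could sit in a full protocol or analysis plan not shown. This also stands. What remains is that the article itself restricts collection to one side and assessment to children who keep the tooth, so a later plan could not use an opposite-side reference without departing from those statements. The plural for the upper molars in Data collection might mean that both sides are measured, but that would conflict with the one-side rule.

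**The main question does not depend on it.** The feared consequence of over-eruption is blocked mesial movement of the lower second molar. Tipping and residual spacing address that by randomised comparison. This is correct, and it limits the importance of the point.

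**The reference is imperfect.** Other treatment continues as normal, so opposite-side teeth may be treated or lost. The number of one-sided cases is not given. Both are real limits on the remedy.

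**Conclusion.** The point holds in a limited form. Over-eruption has no trial-side control value for children treated as allocated, so it does not belong under a between-arm lead-in. As written, change since baseline on one side of the mouth cannot separate normal growth and eruption from the effect of the missing opponent.

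The size of the confounding cannot be stated, because the documents give no amount of normal movement. A reader might scale an assumed 0.5 to 1.5 mm against the 1.44 mm excess (0.5/1.44 = 35%; 1.5/1.44 = 104%). That ratio says nothing reliable about this trial: the numerator is a guess and the denominator comes from adults in a cross-sectional study.

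This is a secondary outcome, and nothing here weakens the primary tipping comparison. The case for a change is that a better measure is available at little cost. It assumes that the opposite-side molar would have moved like the trial-side molar had both kept their opponents.

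**What to change.** 1. On the scanned upper models, also measure the opposite-side upper FPM where it remains present and opposed, that is, in children with one lower FPM extracted.
2. In intervention-arm children of this kind, report trial-side minus opposite-side movement with a 95% CI. Use the opposite-side tooth in the corresponding control-arm children as a supporting reference for normal growth.
3. In children with both lower FPMs extracted, report movement as descriptive only, and state that it cannot be attributed to the missing opponent.
4. Amend the one-side rule in Interventions and the restriction in Data collection to permit these measurements. Move over-eruption out of the between-arm list in Data management and statistical methods, and mark secondary outcome 1 as an intervention-arm outcome.

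If no reference is added, the minimum is to label the outcome as one-arm and descriptive.

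**Cost.** Upper and lower impressions are already planned for all children at all three visits and the models are to be scanned, so the extra work is landmarking, including on control-arm upper models. Children with both lower FPMs extracted cannot contribute to the within-child estimate, nor can those whose opposite-side teeth are lost or treated during follow-up. The usable number is not stated, so the precision of the estimate cannot be given in advance.
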